#### INVESTIGATIONAL MEDICINAL PRODUCT (IMP)

Test Product: Ropivacaine

Pharmaceutical Form: Solution for infusion

Route of Administration: Administered intraperitoneally during and for 72 h after surgery.

Dose:

During surgery: 240 mg

Postoperatively: 720 mg during 72 hours

Total dose (maximal): 960 mg

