**Table 1. Time interval from surgery to start of chemotherapy by treatment arm, IPLA randomized pilot study**

| Variable, Median (IQR*)                              | IPLA (n=20) | Control (n=20) | p-value  |
|------------------------------------------------------|-------------|----------------|----------------------|
| Time-interval surgery to start of chemotherapy, days | 21 (20-29)  | 30 (21-40)     | 0.02                 |
| Length of hospital stay, days                        | 14 (10-17)  | 12 (9-14)      | 0.23                 |

\*IQR= 25th to 75th percentile. Mann-Whitney U test

In this small study, we did not find any difference in plasma cytokines between the groups (fig 2). A maximum dose of Ropivacaine was administered (epidural and intraperitoneal) during 24 h but plasma concentrations of LA measured after 6, 24 and 48 h remained far below known toxic concentration in humans in this study. Additionally, intraperitoneal LA suppressed the serum cortisol at 6 h, but not at 24 h (results not presented here). We are currently studying 3-5 years' survival in these patients.

[figure not shown]

Figure 2. Plasma cytokine concentrations in patients receiving intraperitoneal LA or placebo are shown.

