# 5 Study treatment

## 5.1 Intervention

**Group IPLA:** Ropivacaine 0.2%. After opening the peritoneal cavity and before any surgical dissection, 40 ml of the Ropivacaine will be rinsed in all quadrants within the abdominal cavity under direct vision after opening the peritoneum in order to achieve uniform spread. This will be repeated on two further occasions, first half way through the surgical procedure as estimated by the surgeon and again before closing the abdominal cavity. After the procedure is completed, a plastic multi-port catheter will be inserted lateral to the surgical incision and placed in a way that the tip of the catheter is in the pelvic cavity and the opposite end brought out through the abdominal wall, lateral to the skin incision and fixed with dressing. Ten ml of the Ropivacaine 0.2% will be injected intermittently every other hour via an infusion pump (CADD-Solis) via a bacterial filter that will be programmed to administer an intraperitoneal infusion of 10 mL Ropivacaine 2mg/ml as a bolus injection every other hour for 72 h postoperatively. 72 hours after the end of the surgical procedure the intermittent infusion ends and the intraperitoneal catheter is removed. The amount of infused Ropivacaine 2mg/ml by intraperitoneal infusion will be recorded and the infusion bags discarded in a secure fashion.

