Post-operative management: All women will be managed in a high-dependency post-operative care unit overnight as appropriate. An epidural infusion containing Ropivacaine 2 mg/ml and Sufentanil 1µg/ml will be administered continuously as per hospital routine (usually 4-14 ml/hour for 3 to 5 days after surgery) for pain management. In case of pain not relieved by epidural analgesia, nurse-controlled intravenous morphine or morphine equivalent as per hospital routine (usually 1-2 mg). Additionally, ten ml of the Ropivacaine 0.2% or 0.9% saline (depending on group allotment) will be injected intermittently every other hour through a bacterial filter and via an infusion pump (CADD-Solis) for 72 h postoperatively. The patients will be transferred to the general ward or later rehabilitation until ready for home discharge, which usually occurs on postoperative day 6 - 14, according to hospital routines. Patients will be followed-up via the hospital journal for later assessment of death at 3- or 5 years after surgery according to existing hospital routines.

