## **6 Routine anesthesia and surgery**

Anesthesia: All patients will be given premedication and intraoperative anesthesia according to standardized protocol at all the participating hospitals. A thoracic epidural will be inserted usually at the Th9-Th11 level before induction of general anesthesia. Usually, during surgery, 0.5% Ropivacaine 3-5 mL/hours will be used for pain management. Intravenous injection of Propofol and Remifentanil or equivalent will be used for induction of anesthesia Maintenance of anesthesia is a combination of epidural and inhalation anesthesia during the surgical

procedure and supplemented with infusion of Remifentanyl or equivalent if needed. To achieve neuromuscular blockade Rocuronium or equivalent will be used and will be monitored with train of four. Mechanical ventilation with oxygen in air will be used. Monitoring will include: arterial radial line, oxygen saturation and ECG monitoring. If needed, goal-directed therapy and invasive monitoring guidance will be used to standardize intraoperative fluid management. Mean arterial pressure will be maintained above 65mmHg. Cardiac index >2.5 or stroke volume variation <15% will be the cut-off for hemodynamic instability and will be treated with fluid substitution. Hypotension will be treated with norepinephrine infusion if needed.

Surgery: Will be performed by as per clinical routine. The study treatment will not interfere with any part of the surgical treatment. If per-operative evaluation excludes the patients from cytoreductive surgery because disease extent and the abdomen is closed without any resection of tumor, the participant is excluded from the IPLA-OVCA trial.

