## 9 Ethical considerations

### 9.1 Risk-Benefit considerations

This study will use an additional drug, ropivacaine, administered intraperitoneally during and after surgery in one group of patients. The drug has been used for > 20 years and is a safe, cheap, long-acting local anesthetic that has analgesic and anti-inflammatory characteristics that can be used for the benefit of patients. It is used for local infiltration, as a spinal anesthetic as well as during nerve blocks. Due to the safety profile of ropivacaine, it has almost completely replaced bupivacaine for routine use, except during spinal anesthesia. There is a risk when using ropivacaine in high doses when local anesthetic toxicity may occur. Symptoms of toxicity include numbness around the mouth, metallic taste on the tongue, light-headedness and later epileptiform seizures. Even hypotension and arrhythmias may occur if cardiovascular manifestations occur due to toxicity. Luckily, these are rare if the drug is administered correctly and in the prescribed maximum doses. However, if the drug is used in doses < 750 mg/day (as recommended by the manufacturers), the risk of systemic toxicity is negligible. In a previous study in 40 patients measuring plasma concentration of ropivacaine following intraperitoneal injection (Fig 3), we found that free plasma concentration of Ropivacaine (that determines toxicity) were much lower than known toxic concentrations in humans and no patient revealed signs or symptoms of systemic LA toxicity (43). In the present study, we plan to use similar doses as we used in this previous study.

[figure not shown]

*Fig 3. Postoperative serum levels of total and free plasma concentration of Ropivacaine in the two groups at 6, 24 and 48 hours after incision.*

There is a potential risk of interaction with opioids and other local anesthetics that may potentiate the effect of ropivacaine. The department is well organized in the potential management of any toxic symptoms and intralipid is easily available and effective.

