There is a theoretical risk of catheter-related abdominal infection, however, in our small pilot study we had no catheter related infection. Since the abdominal catheter is inserted under sterile conditions during surgery and a bacterial filter is always used when injecting LA, we do not anticipate any additional risks for participants. However, the patients will be followed-up closely to detect any evidence of infectious complications and start antibiotic management early, if a catheter-related infection is suspected.

In summary, and if our hypothesis is proven correct, it is very much to the advantage for women with advanced EOC subjected to surgery to administer LA, since it may lead to earlier recovery and start of adjuvant chemotherapy. The administration of LA is easy and Ropivacaine is a cheap drug with low toxicity and very few known side effects. The benefits of LA intraperitoneally, if proved, far outweigh the small risk (if any) of systemic toxicity.

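### Section 9.1 ties negligible toxicity to < 750 mg ropivacaine per day, but intraperitoneal plus routine epidural dosing can take the active arm above that: 512–992 mg in the 24 h from the closing dose, 432–912 mg in later 24 h periods

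*Protocol*

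**What the plan says.** Section 9.1 describes the safety of ropivacaine in general terms and attaches a condition on daily dose: "if the drug is used in doses < 750 mg/day (as recommended by the manufacturers), the risk of systemic toxicity is negligible". It then reports the 40-patient pilot, in which free plasma concentrations were well below toxic levels and no patient showed toxicity, and adds: "In the present study, we plan to use similar doses as we used in this previous study". It concludes that the benefits, if shown, would "far outweigh the small risk (if any) of systemic toxicity".

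The active arm receives ropivacaine by two routes.

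- **Intraperitoneal.** Section 5.1 gives three 40 ml doses of 2 mg/ml during surgery, then "10 mL Ropivacaine 2mg/ml as a bolus injection every other hour for 72 h postoperatively". The IMP section lists 240 mg and 720 mg, and states "Total dose (maximal): 960 mg".
- **Epidural, both arms.** Section 6: "Usually, during surgery, 0.5% Ropivacaine 3-5 mL/hours will be used for pain management". Section 5.3: a 2 mg/ml infusion "will be administered continuously as per hospital routine (usually 4-14 ml/hour for 3 to 5 days after surgery". Section 4.3 excludes patients with a contraindication to epidural anesthesia.

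On the pilot, section 1.1.6 says "A maximum dose of Ropivacaine was administered (epidural and intraperitoneal) during 24 h", with plasma concentrations at 6, 24 and 48 h far below toxic. It gives no amount in mg.

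**The concern.** The 750 mg/day statement reassures only if the dose that patients actually receive is below it. The single maximum in the Protocol, 960 mg, covers the intraperitoneal route alone and the whole course of treatment, so it cannot be compared with a daily figure. No section gives a combined daily total or a combined limit.

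The benefit–risk conclusion in 9.1 has two supports: the daily-dose statement and the pilot plasma data. If the combined dose can pass 750 mg, the first does not cover the whole active arm. The second is given without the dose that would show what it covers. Every input is printed in sections 5.1, 5.3 and 6, but an ethics committee or a site has to do the sum itself to notice this.

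**Working it through.** **Inputs**
- Intraperitoneal in surgery: 3 × 40 ml × 2 mg/ml, i.e. 80 mg per dose (5.1, 5.3).
- Intraperitoneal after surgery: 10 ml × 2 mg/ml = 20 mg every 2 h for 72 h, an average of 10 mg/h (5.1).
- Epidural in surgery: 5 mg/ml × 3–5 ml/h = 15–25 mg/h (6).
- Epidural after surgery: 2 mg/ml × 4–14 ml/h = 8–28 mg/h (5.3).

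**The plan's own figure.** 3 × 40 × 2 = 240 mg; 36 boluses × 20 mg = 720 mg; 240 + 720 = 960 mg. This reproduces the IMP section exactly.

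**Active arm, any later 24 h up to 72 h**
- Intraperitoneal: 12 × 20 = 240 mg.
- Epidural: 8 × 24 = 192 mg to 28 × 24 = 672 mg.
- Sum: 432–912 mg.
- Epidural rate at which the sum is 750 mg: (750 − 240)/(2 × 24) = 510/48 = 10.6 ml/h.

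**Active arm, 24 h from the closing intraperitoneal dose** (pump and postoperative epidural taken to start at closure)
- 80 + 240 + 192 = 512 mg to 80 + 240 + 672 = 992 mg.
- Rate at 750 mg: (750 − 320)/48 = 430/48 = about 9.0 ml/h, the midpoint of 4–14 ml/h.

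Neither result needs an operation length.

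**Active arm, first 24 h from the start of surgery.** The Protocol gives no operation length S, so S = 4, 6 and 8 h are assumptions.

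Dose = 240 + 10 × (24 − S) + (15 to 25) × S + (8 to 28) × (24 − S)

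| S (assumed) | Intraperitoneal | Epidural | Combined | Postoperative epidural rate at 750 mg |
|---|---|---|---|---|
| 4 h | 440 mg | 220–660 mg | 660–1,100 mg | 210/40 to 250/40 = 5.3–6.3 ml/h |
| 6 h | 420 mg | 234–654 mg | 654–1,074 mg | 180/36 to 240/36 = 5.0–6.7 ml/h |
| 8 h | 400 mg | 248–648 mg | 648–1,048 mg | 150/32 to 230/32 = 4.7–7.2 ml/h |

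The rate in the last column is (750 − intraperitoneal − epidural in surgery)/(2 × (24 − S)). At mid-range rates (4 ml/h in surgery, 9 ml/h after) the dose is 240 + 20S + 28 × (24 − S): 880 mg for S = 4 and 848 mg for S = 8. Widening S to 2–12 h gives 636–1,126 mg, which still spans 750 mg.

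**Control arm (epidural only).** The first 24 h is the epidural column above, at most 660 mg for S = 4–8 h. Later 24 h periods give 192–672 mg. Reaching 750 mg would need 750/48 = 15.6 ml/h, above the stated range. Only the active arm can therefore pass 750 mg at the printed rates.

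**The case against.** The strongest reply is that 9.1 does not contradict itself. The 750 mg sentence is conditional and sits in a general description of the drug. It sets no trial limit and does not say that the combined trial dose is below 750 mg. The trial-specific argument is the next one: plasma levels measured in a pilot that used both routes, with free concentration named as what determines toxicity. That is more direct evidence than a sum of milligrams. Section 9.1 also recognises interaction with other local anesthetics and says that intralipid is available. Sections 5.3 and 6 provide for high-dependency care overnight as appropriate and for intraoperative ECG and arterial monitoring.

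Most of this stands, and it lowers the weight of the point. It does not remove it. Because the pilot dose is not printed in mg, the Protocol does not show that similar dosing reaches 912 or 992 mg in 24 h. Table 1 shows that 20 of the 40 pilot patients were in the intraperitoneal ropivacaine group, and sampling is reported to 48 h while dosing runs to 72 h.

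A reader might infer more than the document supports:

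- **That the plan breaks a limit of its own.** It sets none.
- **That active-arm patients generally exceed 750 mg.** The epidural rates are what is usual under hospital routine, no distribution is given, and the low end of every range is below 750 mg.
- **That 960 mg is itself above the daily level.** It is a total for surgery plus 72 h; the intraperitoneal drug alone stays below 750 mg in any 24 h.
- **That the pilot dose was too low to support this trial, or that patients would be harmed.** Nothing in the document shows either.

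**Conclusion.** The point holds as a correction to the safety text and should be fixed. At the printed rates the < 750 mg/day condition is not reliably met in the active arm, and the randomised drug makes the difference. The two results that need no operation length carry the conclusion. The first-24-h range of about 650–1,100 mg is secondary because it depends on an assumed 4–8 h of surgery.

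The conclusion takes the usual epidural rates at face value, and takes the 750 mg figure as the Protocol reports it. The frequency of exceedance cannot be stated. No toxicity, and no effect on time to chemotherapy or its analysis, is shown. The pilot may well cover these doses; the text does not let the reader confirm it.

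**What to change.** In section 9.1:

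1. State combined intraperitoneal plus epidural ropivacaine in mg per 24 h by arm, for the period around surgery and for later days to 72 h.
2. Say that the < 750 mg/day statement does not cover the upper part of the active-arm range.
3. Rest the safety case on the pilot's combined-route plasma data and print the pilot's dose in mg per 24 h.
4. Plan a summary of combined 24-h ropivacaine exposure by arm, from the pump records in 10.4 and the medication records in 10.5, making sure epidural volume per 24 h is captured. The sum needs the allocation, so it should be made by unblinded staff or after the code is opened.

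The cost is a text amendment and a check of the existing record forms, with no added patients, visits or procedures.

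A combined daily limit arises only if the pilot dose does not cover these totals. It would act through the epidural rate and would have to be identical in both arms so that blinding holds. Its price is less epidural analgesia and possibly more rescue morphine, so it is a clinical decision for the sponsor.

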## **9.2 Institutional review board/Ethics committee**

The study protocol, patient information and informed consent form will be submitted to the ethics committee for approval. The study will only commence after approval by the ethics committee. All substantial protocol modifications must be submitted to the appropriate Independent Ethics Committee or Institutional Review Board for information and approval before implementation. Once approved by the appropriate Independent Ethics Committee or Institutional Review Board, the investigator shall implement such Protocol modifications. Protocol modifications for urgent safety matters shall however be directly implemented

## **9.3 Informed consent and withdrawal**

Before inclusion in the study, patients will be given oral and written information of the study aims, all treatment procedures and expected and possible adverse events. They will be informed as to the strict confidentiality of their patient data, and that the medical records will be reviewed by their treating physician and study personnel only. The patient is at any time, with or without given reason free to withdraw their consent to study participation, and this choice will not affect their subsequent treatment options or care. Written Informed Consent must be obtained from all participants before enrolment in study. The Informed Consent Form should also be signed at the same occasion by the investigator who gave the written and verbal information. The Informed Consent Form should be filed in the Investigator's File and one copy should be given to the study participant. The study participants will consent to: participate in the study; regulatory authorities and sponsor's representative (e.g. monitor) to gain full access to hospital records, to control the data collected in the study; recording,

collecting and processing data and storing data in a database; and storing of study samples in a biobank (if the participating center is part of the translational part of the IPLA-OVCA trial).

#### **9.4 Premature study termination**

Premature termination of this clinical study may occur because of a regulatory authority decision or drug safety problems.

If, in the opinion of the Investigator, the clinical observations in the study suggest that it may be unwise to continue the study at the site, the Investigator may terminate participation in the study for ethical, safety, or administrative reasons.

If the study is prematurely terminated, the Investigator should promptly inform the patients and take necessary steps to finalize their engagement in the study. All relevant study material must be collected, and accountability completed.

#### **9.5 Patient protection and Good Clinical Practice**

The responsible investigator will ensure that the study is conducted in agreement with the study protocol, ICH-GCP, the declaration of Helsinki and/or Swedish/National laws and regulations; whichever provides the greatest protection for the patient. The participant should be clearly informed that the data collected in the study will not identify any subject taking part in the study following the General Data Protection Regulation (GDPR) (EU 2016/679).

Participating women will be treated according to the international guidelines on GCP as defined by the European Parliament (EG596/200).

#### **9.6 Subject identification**

Participating patients will be identified by a study specific code consisting of a two to six-digit number. This code will be used when registering the patient into the study database. The woman's national identification number will not be entered into the database. The key to the code will be available to the investigator only.

## **10 Investigational Medicinal Products**

### **10.1 Description of Investigational Medicinal Products**

Reference is made to the SmPCs for further information regarding Ropivacaine. For details about dose and administration see section 5.1-5.3.

The study drugs are provided in full by the investigator. The manufacturer does not supply the pharmacological compound.

## 10.2 Packaging, Labeling, Storage and Handling of Investigational Medicinal Products

The IMP: s are used according to clinical routine and only the health personnel will dispense the drugs. The study drugs will be kept in a bag with only the study number. The participants and the health care professionals involved in patient care will therefore be fully blinded until the study is completed. Both Ropivacaine 0.2% and saline are colorless and transparent and therefore full blinding will be possible until study completion. The syringes (three per subject) will be labeled with study name, principal investigator, randomization number, who prepared the IMP/placebo, time and date of preparation, signatures of both persons involved in the preparation (please see separate enclosure). The syringes will also be labeled with either of the number 1, 2 or 3 to indicate the order of doses. The bag for infusion will be covered by an additional bag to shield the original labeling, this outer bag will be labeled with study name, principal investigator, randomization number, who prepared the IMP/placebo bag, time and date of preparation, signatures of both persons involved in the preparation.

**For further information regarding storage and handling reference is given to the SmPC.**

## 10.3 Placebo

Reference is made to the SmPCs for further information regarding 0.9% saline, which will be handled and labelled in the same way as Ropivacaine.

## 10.4 Drug accountability

The investigator is responsible for ensuring IMP accountability. The dispensing of the IMP/placebo will be carefully recorded at the site on the appropriate drug accountability forms and an accurate accounting will be available for verification by the monitor at each monitoring visit. IMP accountability records will include:

- The use of each dose by each subject. For injections, the volume injected will be documented as recorded by the infusion pump
- Randomization confirmation
- The disposition of unused IMP
- Dates, quantities, batch numbers, expiry dates and the patient IDs assigned

The investigator should maintain records that adequately document that the IMP was provided to the subjects in the doses specified by the protocol/amendment(s) and randomization.

IMP, which has been dispensed to a subject, must not be re-dispensed to a different subject.

The monitor will periodically control the IMP accountability forms.

### **10.5 Concomitant Medication**

All concomitantly administered medication during the study will be registered including, but not limited to, sedatives and anti-emetics given postoperatively. Prescription and non-prescription medications used at home after discharge and during the study will also be registered.

The investigator should instruct the patient to notify the study site about any new medications he/she takes after the start of the study drug. All medications and significant non-drug therapies (including physical therapy and blood transfusions) administered after the patient starts treatment with study drug must be listed in the CRF and medical records. The patients will record all additional prescription drugs used after home discharge in their diary.

